## **5. Relevance of the present study**

Although several factors have been associated to sleep disturbances in ICU patients, a recommendation about the best strategy to improve sleep and re-establish the circadian rhythm has not yet been made. As sleep deprivation in ICU may contribute to relevant clinical outcomes, effective strategies to improve sleep are worth to be investigated. We propose an interdisciplinary and pragmatic approach which targets different environmental factors, and which integrates experts from different fields. Although the concepts of dynamic light and sound masking are well known, our proposal includes the local design of solutions based on these concepts. We also chose to use the highest standard for sleep measurements (PSG), which has been one of the major limitations of previous research in this field.

We expect that our intervention will be effective to improve sleep. Although this study is underpowered to study potential impacts of the strategy on mortality or ICU length of stay, if the intervention proves to be effective in improving sleep, a larger scale study could follow. But even if the intervention proves not to be effective, the data collected about sleep and about long-term neuropsychologic outcomes in our ICU population will be highly relevant to advance our understanding about the relation between these variables, and for the planning of future studies.

## **II. Hypothesis and objectives**

### ***Hypothesis***

In critically ill patients, the use of a multifaceted intervention of environmental control in the ICU, based on dynamic light therapy, auditory masking, and rationalization of ICU nocturnal patient care activities, is

associated with improved quantity and quality of sleep assessed by polysomnography and other semi-quantitative methods, compared to standard care.

### **General goal**

To compare the effects of the use of a multifaceted intervention of environmental control in the ICU, based in dynamic light therapy, auditory masking, and rationalization of ICU nocturnal patient care activities, versus standard care, on quantity and quality of sleep, on delirium, and on post-intensive care neuropsychological impairment, in critically ill patients.

### **Specific goals**

1. To compare the effects of the use a multifaceted intervention of environmental control in the ICU versus standard care, in quantity and quality of sleep by PSG and actigraphy, and by questionnaires, during the whole stay in ICU or up to day 30, and at hospital discharge and 6 months after ICU discharge.
2. To compare the effects of the use a multifaceted intervention of environmental control in ICU versus standard care, in the oscillation of plasma concentrations of Melatonin and Cortisol during the ICU at days 1 and 3 after randomization.
3. To compare the acute effects of the use a multifaceted intervention of environmental control in the ICU versus standard care, on prevalence and duration of delirium during ICU stay.
4. To compare the effects of the use a multifaceted intervention of environmental control in the ICU versus standard care, in neuropsychological impairment (depressive symptoms and cognitive impairment) at 6 months after ICU discharge.

### **Primary outcome**

- 1) Sleep quantity (time in slow wave sleep-N3 and time in Rapid eye movement-REM) assessed by PSG at day 3

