#### **d. Randomization**

Patients who meet criteria and who are hospitalized in a modified ICU room will be invited to participate in the study. However, if a patient meets criteria, but is placed in another room, he/she can be transferred to any of the modified rooms if any of them is free. Once the Informed Consent signature is obtained, patients will be randomized to receive a multifaceted intervention of environmental control in the ICU (dynamic light therapy, auditory masking, and rationalization of ICU nocturnal patient care activities) (intervention group) or standard care (control group). The randomization sequence will be generated by a computer program with an allocation 1:1. Due to the type of intervention under study the patient and the research team can't be blinded to the group assignment. Nonetheless, statisticians and the researchers responsible for analysis of PSG and actigraphy, as well as those performing long-term outcome assessments will be blinded to the group allocation.

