### ***g. Sample size and statistical analysis***

According to a previous study, which measured sleep with PSG (63), and other studies, which have described sleep architecture in the ICU (3-7), we estimate that the N3 stage time in our study population will be 7 minutes with a SD of 9 minutes. We considered that a 50% improvement in N3 stage time would be both, clinically relevant and realistic. With a power of 80% and with alpha of 5%, we calculated that a sample size of 56 patients is required to demonstrate statistically significant differences.

General statistical analysis will be performed according to intention to treat. Baseline characteristics will be reported using mean values  $\pm$  standard deviation (SD), or median (p25-75) and proportions where

appropriate. The use of parametric vs non-parametric tests will be decided according to data distribution and the fulfillment or not of normality assumptions. Specific statistical analysis for comparisons between groups will be performed by Student's-t test or Mann-Whitney U-test for continuous variables, and by chi-square for proportions. Changes along time will be analyzed by one-way (repeated-measures) analysis of variance (ANOVA) or Friedman test. Interactions between groups and time we will assessed with two-way repeated-measures ANOVA. All statistical calculations will be performed using Stata Statistical Software, Release 15.1 (College Station, TX). A probability value (p-value) of less than 0.05 will be considered as statistically significant.

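### The primary outcome is two sleep variables, the trial is sized on one of them, and no rule says which result counts as success

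*Protocol*

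**What the plan says.** The Primary outcome section of the protocol has one numbered entry: "Sleep quantity (time in slow wave sleep-N3 and time in Rapid eye movement-REM) assessed by PSG at day 3". It is labelled as sleep quantity and defined by two stage times.

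Section g, Sample size and statistical analysis, deals with one of the two:

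- Control value: "we estimate that the N3 stage time in our study population will be 7 minutes with a SD of 9 minutes".
- Target effect: "We considered that a 50% improvement in N3 stage time would be both, clinically relevant and realistic".
- Result: "With a power of 80% and with alpha of 5%, we calculated that a sample size of 56 patients is required".

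No mean, SD or effect is given for REM time, or for N3 and REM combined.

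On testing, the same section says that "comparisons between groups will be performed by Student's-t test or Mann-Whitney U-test for continuous variables", and closes with "A probability value (p-value) of less than 0.05 will be considered as statistically significant". It gives no order of testing, no division of alpha, and no statement that both stages must succeed.

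**The concern.** A primary outcome should fix in advance which result makes the trial positive. Here three readings are open: either stage suffices, both must be significant, or the two times are added and tested once. They carry different error rates and different sample sizes, and the protocol's alpha and sizing statements were written for one variable only.

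A split result is not far-fetched. The section on normal sleep gives the two stages different roles: physical repair for N3, memory consolidation for REM. The section on environmental strategies reports that earplugs and masks raised REM sleep in healthy people in a simulated ICU, and that a randomized ICU trial of the same devices did not change the proportion of N3. The populations differ, so this is not evidence about this trial, but it shows that the stages need not move together. If they diverge, the plan has no answer. The blinding of PSG scorers and statisticians protects measurement. It does not settle which stage was meant to decide once the results are known.

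**Working it through.** **Inputs (Protocol, section g, unless noted).** Control N3 time 7 min, SD 9 min; 50% improvement, so a difference of 0.5 × 7 = 3.5 min; power 80%; alpha 5%; total 56. Allocation is 1:1 (section d, Randomization), so 28 per arm. Sidedness is not stated; two-sided is assumed. The correlation between the N3 and REM test statistics is not given, so a range is assumed.

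**The plan's own figure.** For two parallel arms, n per arm = 2 × (1.960 + 0.842)² × 9² / 3.5² = 103.8, so 104 per arm and 208 in total. The stated 56 is not reproduced. A one-sided 5% test would need 82 per arm (164 in total). With 28 per arm the noncentrality is (3.5/9) × √14 = 1.455, which gives about 31% power two-sided (42% one-sided). This is a separate fault. It is shown because it limits what any fix here can achieve.

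**Reading 1: either stage suffices, each tested at 5%.** With independent tests, the family-wise error is 1 − 0.95² = 0.0975. For correlated tests, it is one minus the bivariate-normal probability that both statistics lie within ±1.96:

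| Assumed correlation | Family-wise error |
|---|---|
| 0 | 9.75% |
| 0.3 | 9.5% |
| 0.5 | 9.1% |
| 0.8 | 7.8% |
| 0.9 | 7.0% |

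The 5% is exceeded throughout this range.

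**Reading 2: both stages required.** A false claim needs a false rejection on at least one stage that is truly null, so the error is at most 5%. If neither stage is affected it is smaller: 0.25% at correlation 0 and 3.0% at 0.9. Power is what suffers. If each test truly had 80% power and the two were independent, joint power would be 0.8 × 0.8 = 64%. Positive correlation raises this, but joint power cannot exceed that of the weaker test. For REM the protocol gives nothing from which power could be computed.

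**Reading 3: one test on N3 plus REM time.** The error is 5%. The sizing would need a mean, SD and effect for the sum, and none is given.

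**Side by side.**

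| Reading | Stated 5% alpha | Stated sizing |
|---|---|---|
| Either | Not held | Built on N3 only |
| Both | Held | No REM inputs; 80% not supported |
| Sum | Held | No inputs for the sum |
| N3 only | Held | Right variable, but 56 does not give 80% |

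Only an N3-only primary outcome uses the variable that section g sized, and the Primary outcome section does not say that.

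**The case against.** The strongest reply is that the protocol nowhere says that either stage suffices. The outcome is one entry joined by a conjunction, the hypothesis is worded conjunctively too, and the p-value sentence is a general threshold, not a success rule. All of that stands. A reader might infer that the trial's false-positive rate is nearly double the stated 5%. The documents do not support this as a fact. It needs an unadjusted either-stage rule and a low to moderate correlation. N3 and REM times come from the same night, and at a correlation of 0.9 the figure is 7.0%.

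A reader might also infer that requiring both stages brings power down to about 9% (independent tests) or 16% (correlation 0.5), from 28 per arm and the N3 effect assumed for REM as well. Those figures mostly reflect the sample-size fault: N3 alone already has only about 31%, and 0.307² = 0.094. The REM effect behind them is an assumption. The cost of the both-stages rule itself is better shown by 64% against 80%.

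A further reply is that testing order and multiplicity are commonly left to the statistical analysis plan. That is fair for the testing procedure. It does not cover the mismatch within the protocol, which defines a two-variable primary outcome and sizes one variable. A later rule of either-with-adjustment or both would also need its own sample size.

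**Conclusion.** The point holds as a mismatch and a missing decision rule. The primary outcome has two components, only one is sized, and the unadjusted threshold does not say how they combine. The stated 5% alpha fails under the either-stage reading (up to 9.75%, and 7.0% at an assumed correlation of 0.9). The stated 80% power is unsupported under the both-stages reading (64% if each independent test had 80%). Sizing inputs are absent if the sum is meant. The error figures rest on two-sided 5% tests, approximate normality of the test statistics and the assumed correlations. It is not established that the error rate is inflated as the protocol stands, because the rule that would inflate it is not written down. Since the gap concerns the primary claim, it should be closed before outcome data are compared by group.

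**What to change.** In the Primary outcome section, name N3 time on the day-3 PSG as the sole primary outcome, as it is the only variable with sizing assumptions. Make REM time on the same recording the first secondary outcome, tested at 5% only if N3 is significant. Otherwise report it with its confidence interval and no claim of significance. This fixed sequence holds the error across the two tests at 5%.

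The cost is about one sentence and one real concession: an effect on REM alone can no longer carry the primary claim. If the sponsor does not want that, the alternatives are valid but need a matching size. Splitting alpha at 0.025 each needs 126 per arm for N3 (252 in total), and 28 per arm would then give about 22% power. Requiring both, with independent tests and the N3 standardised effect assumed for REM, needs √0.8 = 89.4% power on each, or 137 per arm (274 in total).

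Naming N3 does not restore 80% power. The 56 patients still give about 31% for the stated effect, and that has to be dealt with separately, starting from about 208.

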### **Secondary outcomes**

- 1) Total time of sleep assessed by actigraphy
- 2) Sleep quality assessed by questionnaires (RCSQ and PSQI)
- 2) Circadian timing: Oscillation of plasma concentration of Melatonin and Cortisol
- 3) ICU delirium (prevalence and duration of delirium in ICU) by Confusion Assessment Method for the ICU (CAM-ICU)
- 4) Neuropsychological impairment (depressive symptoms and cognitive impairment) at 6 months post ICU discharge by cognitive testing and instrument screens of depression

## **III. Methodology**

### **a. Study design**

Prospective, parallel-group, randomized trial in critically ill patients. Our project will follow the CONSORT (64) guidelines for this class of studies.

### **b. Setting**

The study will be performed at the polyvalent Intensive Care Unit of University Hospital of the Pontificia Universidad Católica de Chile. In particular, four of the 32 rooms will be modified during the first months of the project to install a parallel lighting system that allows the application of dynamic lighting, and an auditory masking system, which will be used in case the patient is randomized to the intervention group (see below).

The study will have to be approved by the Institutional Review Board of the Facultad de Medicina UC. A signed informed consent will be asked to the next of kin of all eligible patients, and confirmed later by the patients when feasible.

### **c. Patients**

Adult patients ( $\geq 18$  years) will be screened for the following inclusion criteria:

#### **Inclusion criteria:**

- Patient under invasive mechanical ventilation for at least 72 hours
- Patient without sedation or with superficial sedation level (SAS 3-4 by Sedation-Agitation Scale [65]), during most of the daytime within the 24 previous hours

#### **Exclusion criteria:**

- Patient who required mechanical ventilation in another episode of hospitalization in the 2 months before screening
- Patients with primary neurological or neurosurgical disease

- Presence of mental or intellectual disability prior to hospitalization or communication/language barriers
- Pre-existing comorbidity with a life expectancy not exceeding 6 months (eg, metastatic cancer)
- Readmission to the ICU (patients can only be included if they are on their first ICU admission of the present hospitalization)
- No fixed address for follow-up
- Patients with moderate to severe visual or hearing impairment
- Patients with known sleep disturbance before hospital admission
- Early limitation of therapeutic effort

#### **d. Randomization**

Patients who meet criteria and who are hospitalized in a modified ICU room will be invited to participate in the study. However, if a patient meets criteria, but is placed in another room, he/she can be transferred to any of the modified rooms if any of them is free. Once the Informed Consent signature is obtained, patients will be randomized to receive a multifaceted intervention of environmental control in the ICU (dynamic light therapy, auditory masking, and rationalization of ICU nocturnal patient care activities) (intervention group) or standard care (control group). The randomization sequence will be generated by a computer program with an allocation 1:1. Due to the type of intervention under study the patient and the research team can't be blinded to the group assignment. Nonetheless, statisticians and the researchers responsible for analysis of PSG and actigraphy, as well as those performing long-term outcome assessments will be blinded to the group allocation.

#### **e. Intervention**

##### **■ Intervention group**

**Lighting:** A dynamic lighting system (DLS) will be implemented. The DLS, on the basis of literature (35,37,39), will automatically modify the different levels of illuminance required and at the same time reproduce the different color temperatures in order to simulate daylight conditions during daytime. The illuminance will vary between 500 to 1,000 lux when looking straight up on the ceiling and 800 to 1,500 lux when looking towards the lamp. The DLS will provide sufficient illuminance for medical inspection ( $\geq 1,000$  lx) even without looking directly into the light source. This system will be composed by:

- a) Four light emitting diode (LED) recessed luminaires of 600x600 mm (PowerBalance RC464B LED80S, Philipps), with adjustable white features from 2700 to 6400 K and different lumen levels up to 8,000 lm (annex 2), which will be placed in the center of the ceiling. A dedicated control system will induce dynamic predefined curves that vary the temperature and intensity of the color temperature according to the hours of the day.
- b) A RGB color system cove perimeter in the ICU room, which provides a basic lighting for night at 20 lux requirement, and other comfort effects (annex 4).
- c) An intelligent control system will be installed which consists of: multipurpose modular room controller, dry-contact interface and LED driver, network power supply, integration devices. The DLS will be controlled from a central module, which will be only accessible by the investigators. The intervention will be completely designed and performed by lighting specialist engineers of Escuela de Diseño of Pontificia Universidad Católica de Chile.

**Noise:** The auditory masking system will provide a continuous background digitally generated broadband (0.5-22.05 KHz) pink noise (50,51). The sound system will be placed near the head of the bed. This will be started (at 62 DB sound level) each night for 8 hours (10:00 pm – 5:00 am). In addition, heart rate, blood pressure and saturation of O2 telemetry alarms will be set to a minimum volume inside the patient's room. The intervention will be completely designed and performed by a sound specialist engineer of the Electrical Engineering Department and Music Institute of the Catholic University of Chile.

**Nocturnal patient care activities:** Starting the first day after inclusion, night-time patient care activities will be re-organized to minimize interruptions. For this purpose, the medication administration schedule will be organized, and the vital signs monitoring will be done continuously by medical devices without requiring to disturb the patient. As in our ICU temperature monitoring is performed with an axillary thermometer every hour, we will install a temperature sensor in the patient's armpit for continuous measurement. Hygiene and comfort activities will be scheduled for daytime. During the day medications, diagnostic imaging, laboratory draws, and care orders will be reviewed and retimed by the research staff in conjunction with the clinical staff. Emergency interventions will not be limited or altered. For patients receiving the intervention, research staff will provide one-to-one coaching to the bedside nurse. Number and length of nurse interventions during the night (from 10:00 p.m. to 8:00 a.m.) will be recorded until ICU discharge by bedside nurses.

#### ▪ **Control group**

**Lighting:** The standard lighting system currently installed in the ICU rooms (annex 1) provides a fix light of 300 to 400 lux during daytime, and 0 to 30 lux during night-time. However, controls are not automatic and therefore it depends on staff whether lights are switched on during daytime and switched off during nighttime. The lighting is composed of:

- a) 3 linear recessed lighting luminaires each with one fluorescent tube of 28W/T5/840, color temperature 4000K, neutral white, and a diffuser of transverse lamellae for glare control protection
- b) 2 pieces of recessed compact fluorescent downlights with luminaires 2x26W/840, color temperature 4000K, neutral white
- c) 1 piece of fluorescent lighting luminaire (kept on for night use) surface mounted to the driver's tray, behind the clinical bed. Fluorescent lamp 14W/ T5/830, color temperature of 3000K, warm white, with opal diffuser.
- d) The lighting control system is an on / off switch, separated into three commands (see annex 1).

**Noise:** The rooms do not have noise isolation. During the night usually the doors of the rooms remain closed. In our ICU there is no protocol for reducing environmental noise. Although we have not recorded noise continuously in our ICU we have registered isolated measurements similar to those reported in the literature (77,78). This is mean average values of 60 dB during daytime and 50 dB during nighttime, but with frequent peaks over 80 to 90 dB

**Nocturnal patient care activities:** There is no specific protocol for the organization of patient care activities during the night. The activities (schedules of drug administration and intravenous infusions, schedules of non-urgent examinations, and non-urgent procedures) are organized during the morning by the patient's nurse according to their own clinical criteria. Hygiene and comfort activities (bathing, linen changes, wound care, dressing changes) are carried out in standard schedules according to the rules of the ICU. Drug administration, examinations and urgent procedures are performed when necessary.

#### ▪ **Common procedures for both groups**

To avoid bias, in both groups the protocol of analgesia and sedation of the unit will be used if the patient requires it. Level of sedation will be monitored as part of daily care by nurses in all patients every four hours using the Sedation-Agitation Scale. In our unit benzodiazepines are not used except when the patient uses them chronically or to avoid drug and alcohol withdrawal syndrome. In case patients admitted to the study present delirium, they will be treated according to the institutional protocol for management of delirium, independent of the study group. In our unit, melatonin and other sleep inducers are not used routinely.

#### **f. Study variables**

- 1. Baseline parameters to be collected:** At the time of enrolment, information collected on each patient will include the following: patient demographics, dates of hospital and ICU admission, illness severity according to the Acute Physiology (APACHE II), Chronic Health Evaluation II and Sequential Organ Failure Assessment Score (SOFA), comorbidities according to the Charlson Comorbidity Index, admission diagnoses, and pre-existing neuropsychological impairment.
- 2. Repeated assessments to be performed during the study protocol:** During the course of each patient's stay in the ICU data will be collected on: Sequential Organ Failure Assessment Score (SOFA), Partial pressure of oxygen (PaO2)/Fraction of inspired oxygen (FiO2), daily arterial pressure and minimum glycemia value obtained, daily doses of medications. Use of hemodialysis and vasopressors, mechanical ventilation duration and ICU/Hospital length of stay data will be collected also. All patients will undergo a standardized follow-up immediately prior to hospital discharge and at 6 months later. At 6 months patients will attend to a follow-up visit, and if they are unable to attend they will be visited at home.

